## 6.8 Laboratory Analyses

Blood samples will be drawn, urine will be collected, and muscle biopsies will be harvested from the subjects as indicated in the Schedule of Assessments. Subjects will be in a fasting state (last food intake at least 12 hours before the visit) prior to all of the blood draws except screening. Additional blood samples may be collected during the course of the study in order to perform or repeat laboratory tests outlined in the Schedule of Assessments if needed.

Protection of subject confidentiality will extend to all data generated from the assaying of these samples. These samples will be alphanumerically coded and the persons performing the analysis will not be aware of the subject's identity.

At Visit 1 (screening), whole blood will be collected and dispensed into the following tubes:

1. Two 4 ml EDTA Tubes:
  - a. One 4 ml EDTA tube will be used for CBC analysis;
  - b. One 4 ml EDTA tube will be used to generate serum for HbA1C levels analysis;
2. One 5 ml SST tube for electrolyte (Na, K, Cl), creatinine, AST, ALT, GGT, BUN and bilirubin analyses.

At Visit 3 (baseline), whole blood, urine and a muscle biopsy will be collected and dispensed into the following tubes:

- A. The whole blood will be dispensed into the following tubes:
  1. Two 2.7 ml light blue top citrate tubes for NAD analysis
  2. One 4ml EDTA Tube for NR metabolite analysis
  3. Two 5 ml SST tubes:
    - a. One 5 ml SST tube will be used for lipid panel analysis and AST, ALT, GGT and BUN Analysis
    - b. One 5 ml SST tube will be used for hsCRP analysis
  4. One 6 ml Green Top tube for Amino Acid analysis
- B. The urine sample will be divided in 5 ml tubes for Niagen metabolite and creatinine analyses and snap frozen in liquid Nitrogen.

At Visit 4 and 5 (Day 7 and 14) whole blood and urine will be collected.

- A. The whole blood will be dispensed into the following tubes:
  1. Two 5 ml SST tubes:
    - a. One 5 ml SST tube will be used for hsCRP analysis;

Protocol 15NRHC: A randomized, double-blind, placebo controlled parallel study investigating the effects of Niagen™ (Nicotinamide Riboside) on Niagen™ metabolites in healthy adults

- b. One 5 ml SST tube will be used for AST, ALT, GGT and BUN analysis; and lipid panel analysis
- 2. One 6 ml Green Top tube for Amino Acid analysis
- 3. Two 2.7 ml light blue top citrate tubes for NAD analysis
- 4. One 4ml EDTA Tube for NR metabolite analysis
- B. The urine sample will be divided in 5 ml tubes for Niagen metabolite and creatinine analyses and snap frozen in liquid Nitrogen.
- C. The muscle biopsy collected at Visit 3 for Niagen metabolite analyses will be snap frozen in liquid nitrogen.

At Visit 6 (Day 28), whole blood and urine will be collected.

- A. The whole blood will be dispensed into the following tubes:
  - 1. Two 5 ml SST tubes:
    - a. One 5 ml SST tube will be used for hsCRP analysis;
    - b. One 5 ml SST tube will be used for electrolyte (Na, K, Cl), creatinine, AST, ALT, GGT and BUN analysis; and lipid panel analysis
  - 2. Three 4 ml EDTA Tubes:
    - a. One 4 ml EDTA tube will be used for NR metabolite analysis
    - b. Two 4 ml EDTA tubes will be used for CBC and Hb1Ac analysis
  - 3. One 6 ml green top tube will be used for amino acid panel analysis
  - 4. Two 2.7 ml light blue top citrate tubes for NAD analysis
- B. The urine sample will be divided in 5 ml tubes for Niagen metabolite and creatinine analyses and snap frozen in liquid Nitrogen.

At Visit 7 (Day 56), whole blood, urine and a muscle biopsy will be collected.

- A. The whole blood will be dispensed into the following tubes:
  - 1. Two 5 ml SST tubes
    - a. One 5ml SST tube will be used for electrolytes (Na, K, Cl), creatinine, AST, ALT, GGT, BUN and bilirubin analysis; and lipid panel analysis
    - b. One 5 ml SST tube will be used for hsCRP analysis.
  - 2. One 6 ml green top tube will be used to generate plasma for amino acid panel analysis.
  - 3. Three 4 ml EDTA tubes.
    - a. One 4 ml EDTA tube will be used for CBC analysis
    - b. One 4 ml EDTA tube will be used to generate serum for HbA1C analysis;
    - c. One 4 ml EDTA tubes will be used for NR metabolite analysis
  - 4. Two 2.7 ml light blue top citrate tubes for NAD analysis
- B. The urine sample will be equally divided into two 5 ml tube for Niagen metabolite and creatinine analyses and snap frozen in liquid Nitrogen.
- C. The muscle biopsy collected for Niagen metabolite analyses will be snap frozen in liquid nitrogen.

For the analysis of NAD, the blood drawn in light blue top tubes will be immediately placed on ice. The tubes should be inverted 4 times then centrifuged at 2000 rpm at 4°C for 5 min. The plasma should be removed and aliquoted into two cryovials. The RBC fraction will be divided into 100uL portions by pipetting the cells into 4 chilled cryovial tubes containing 1ml of cold 0.5M perchloric acid. The tubes should be inverted 4 times then immediately frozen and stored at -80°C.

Protocol 15NRHC: A randomized, double-blind, placebo controlled parallel study investigating the effects of Niagen™ (Nicotinamide Riboside) on Niagen™ metabolites in healthy adults

For the NR metabolite analysis, the blood drawn in EDTA tubes will be inverted and aliquoted into two 2ml cryovials and stored at -80°C.

Blood, muscle biopsies, and urine will be stored at -80°C and analyzed for Niagen™ metabolites (nicotinamide adenine dinucleotide (NAD), nicotinamide (Nam), N-methyl-2-pyridone-3/5-carboximide (2-PY), and methylnicotinamide (meNam)) at a laboratory of the sponsor's choosing. Urine samples will also be analyzed for creatinine; analysis of Niagen™ metabolites in urine will be standardized to creatinine concentrations.

Individuals performing the bioanalysis of study samples will remain blinded towards the dose of the investigational product that the participants receive.

The total blood volume collected for the laboratory assessments listed above will be approximately 156 ml over the period from screening to end of study. At any study visit, blood loss per subject is not expected to exceed approximately 33.4 ml.

LifeLabs Medical Laboratory Services in London, Ontario, Canada will be used in this study to measure safety laboratory parameters.

## **6.9 Termination of the Trial**

In the case of premature termination of the trial, participating investigators/participants, and the Institutional Review Board must be promptly informed of the termination.

## **6.10 Protocol Amendments**

If amendments to the study protocol are required after approval such changes will be captured in writing the reasons for the change documented and signed and dated by the sponsor. Any such amendments may be subject to IRB and Health Canada review/approval prior to implementation. Exception: if it becomes necessary to alter the protocol to eliminate an immediate hazard to patients, an amendment may be implemented prior to IRB approval. In this circumstance, the Investigator must notify IRB and Health Canada in writing within five (5) working days of the implementation.

## **7 Safety Instructions and Guidance**

### **7.1 Adverse Events and Laboratory Abnormalities**

#### **7.1.1 Adverse Events**

An adverse event (AE) is any untoward medical occurrence in a clinical investigation subject who has been administered an investigational product and which does not necessarily have a causal relationship with this treatment. An AE can be any unfavorable and unintended sign (including an abnormal laboratory finding), symptom, or disease temporally associated with the use of a product, whether or not it is considered related to that product. Pre-existing conditions which worsen during a study are to be reported as AEs.

During the study, subjects should record any adverse effects in their diary. At each visit the subject will be asked "Have you experienced any difficulties or problems since I saw you last"? Any adverse events (AEs) will be documented and in the study record and will be classified

Protocol 15NRHC: A randomized, double-blind, placebo controlled parallel study investigating the effects of Niagen™ (Nicotinamide Riboside) on Niagen™ metabolites in healthy adults

according to the description, duration, intensity, frequency, and outcome. The investigator will assess any AEs and decide causality.

Intensity of AEs will be graded on a three-point scale (mild, moderate, severe) and reported in detail in the study record.

|           |                                                                  |
|-----------|------------------------------------------------------------------|
| Mild:     | Awareness of event but easily tolerated                          |
| Moderate: | Discomfort enough to cause some interference with usual activity |
| Severe:   | Inability to carry out usual activity                            |

The causality relationship of investigational product to the adverse event will be assessed by the investigator as either:

|                |                                                                                                                                                                                                                 |
|----------------|-----------------------------------------------------------------------------------------------------------------------------------------------------------------------------------------------------------------|
| Most probable: | There is a reasonable relationship between the investigational product and AEs. The event responds to withdrawal of investigational product (dechallenge) and recurs with rechallenge when clinically feasible. |
| Probable:      | There is a reasonable relationship between the investigational product and AEs. The event responds to dechallenge.                                                                                              |
| Possible:      | There is a reasonable relationship between the investigational product and AEs. Dechallenge information is lacking or unclear.                                                                                  |
| Unlikely:      | There is a temporal relationship to the investigational product administration but there is no reasonable causal relationship between the investigational product and the AEs.                                  |
| Not related:   | No temporal relationship to the investigational product administration or there is a reasonable causal relationship between non-investigational product, concurrent disease or circumstance and the AEs.        |

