### 3 STUDY DESIGN

[figure not shown]

This will be a randomized, double blind, placebo controlled, 4-arm parallel study that will investigate the effect of Niagen™ supplements in healthy subjects on Niagen™ metabolite concentrations in urine, blood, and muscle in healthy males and females.

The planned sample size for this study is 140 healthy males or females, with 35 subjects randomized equally to each of the four study arms in a double-blind manner at a ratio of 1:1:1:1.

| Study Arm      | Subject Number |
|----------------|----------------|
| Niagen™ 100mg  | N = 35         |
| Niagen™ 300mg  | N = 35         |
| Niagen™ 1000mg | N = 35         |
| Placebo        | N = 35         |
| Total   | N = 140 |

In order to evaluate primary, secondary, exploratory, and safety outcomes, study assessments will be conducted at baseline and all study visits. At each visit to the clinic, whole blood (which will be centrifuged and separated into WBC, RBC and plasma fractions) and urine will be collected from each participant for NR metabolite and creatinine analysis. REE will also be calculated at baseline and all subsequent clinic visits using indirect calorimetry. A muscle biopsy will be collected at baseline and end of study (week 8).

The study will be conducted at a single site in London, Ontario.

Protocol 15NRHC: A randomized, double-blind, placebo controlled parallel study investigating the effects of Niagen™ (Nicotinamide Riboside) on Niagen™ metabolites in healthy adults

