### 6.3 Visit 3 – Baseline (Day 0)

Eligible participants will return to the clinic in the morning, after fasting for 12 hours (nothing to eat or drink except water) for baseline assessments. Participants must not have consumed caffeine or exercised on the day of the visit, prior to the visit.

1. Review of medical history and concomitant therapies and current health status
2. A physical exam will be conducted
3. Participants will be randomized into the study.
4. Participants will be weighed and BMI will be calculated
5. Resting blood pressure and heart rate will be measured
6. REE will be evaluated
7. Study diaries and 3-Day Food Records will be collected and reviewed. Subjects will receive dietary counselling from a dietician.
8. Collect pre-dose urine sample for the measurement of Niagen™ metabolites and random urine creatinine analysis
9. Collect pre-dose blood for measurement of Niagen™ metabolite
10. Collect pre-dose blood samples for lipid panel, amino acid panel, hsCRP, AST, ALT, GGT and BUN
11. Collect muscle biopsy from the *Vastus Lateralis* of subject's leg for Niagen™ metabolite analyses.
12. New study diaries and 3-Day Food records will be dispensed to the participant. 3-Day Food records will be completed every week until the next visit, and the study diary will be completed daily.
13. Investigational product will be dispensed according to the randomization schedule.
14. After all assessments are completed the participant will take the first dose (4 capsules) of the product at the clinic.
15. Participants will be instructed in detail by site personnel about the treatment regimen.
16. The next visit will be scheduled for Day 7 this visit ( $\pm$  3 days).

Protocol 15NRHC: A randomized, double-blind, placebo controlled parallel study investigating the effects of Niagen™ (Nicotinamide Riboside) on Niagen™ metabolites in healthy adults

Study staff will be in contact with the subject weekly to facilitate dietary compliance.

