### 6.7.3 Micro-Needle Muscle Biopsy

Micro-needle muscle biopsies will be performed once at the Baseline visit (Visit 3, Day 0) once at the End of Study Visit (Visit 7, Day 56). Prior to the procedure, the Qualified Investigator, or designate, will ensure that the subject has completed the Muscle Biopsy Screening Form and has read and signed the Muscle Biopsy Information Sheet and fully understands the nature of the procedure and any associated risks.

The biopsy samples will be taken from the *Vastus Lateralis* muscle by an experienced physician or trained delegate. The surface area where the micro-needle will be inserted will be disinfected and anesthetized using a local anesthetic. A cannula will be used to pierce the skin and a micro-needle will be inserted. Following collection of the muscle sample, the needle will be removed and pressure will be applied to the area where the needle was inserted for a few minutes until any bleeding stops. The wound will then be treated and bandaged appropriately.

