### **7.1.2 Serious Adverse Event**

A serious adverse event (SAE) is any experience that suggests a significant hazard, contraindication, side effect or precaution. It is any AE that results in any of the following outcomes:

- Death
- A life-threatening adverse event
- Inpatient hospitalization or prolongation of existing hospitalization
- A persistent or significant disability or incapacity
- A congenital anomaly/birth defect in the offspring of a subject who received the study treatment
- Important medical events that may not be immediately life-threatening or result in death or hospitalization but may jeopardize the subject or may require intervention to prevent one of the outcomes listed above. Examples of such events are intensive treatment in an emergency room or at home for allergic bronchospasm; blood dyscrasias or convulsions that do not result in hospitalization; or the development of drug dependency or drug abuse.

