#### **8.2 Analysis Plan**

- The **Safety Population** will consist of all subjects who received any amount of either product, and on whom any post-randomization safety information is available.

Protocol 15NRHC: A randomized, double-blind, placebo controlled parallel study investigating the effects of Niagen™ (Nicotinamide Riboside) on Niagen™ metabolites in healthy adults

- The **Intent-to-Treat (ITT) Population** consists of all subjects who received either product, and on whom any post-randomization efficacy information is available.
- The **Per Protocol (PP) Population** "Per Protocol (PP) Population" consists of all subjects who consumed at least 80% of treatment or placebo doses do not have any major protocol violations and complete all study visits and procedures connected with measurement of the primary variable.

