| High sensitivity C-reactive Protein                                                                             |   |   | X | X | X | X | X |
| Resting Metabolic Rate                                                                                          |   |   | X | X | X | X | X |
| Dietary Counseling from a dietician                                                                             | X | X | X | X | X | X |   |
| 3-Day Food Records dispensed                                                                                    |   | X | X | X | X | X |   |
| 3-Day Food Records returned                                                                                     |   |   | X | X | X | X | X |
| IP dispensed                                                                                                    |   |   | X | X | X | X |   |
| IP returned                                                                                                     |   |   |   | X | X | X | X |
| Treatment diary dispensed                                                                                       |   | X | X | X | X | X |   |
| Treatment diary returned                                                                                        |   |   | X | X | X | X | X |
| Run-In diary dispensed                                                                                          |   | X |   |   |   |   |   |
| Run-In diary returned                                                                                           |   |   | X |   |   |   |   |
| Compliance calculated                                                                                           |   |   | X | X | X | X | X |
| Adverse events assessed                                                                                         |   |   |   | X | X | X | X |

Protocol 15NRHC: A randomized, double-blind, placebo controlled parallel study investigating the effects of Niagen™ (Nicotinamide Riboside) on Niagen™ metabolites in healthy adults

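### Day 0 biopsy harms that begin and resolve before the first dose, or occur in a subject never dosed, fall outside the AE and SAE definitions, and the protocol conflicts with itself on AE collection at Visit 3

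*Protocol*

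**What the plan says.** **Definitions.** Protocol section 7.1.1 describes an AE as "any untoward medical occurrence in a clinical investigation subject who has been administered an investigational product", whether or not the product caused it. Section 7.1.2 opens with a broad sentence about experiences that suggest a hazard, then gives the working criterion for an SAE: "It is any AE that results in any of the following outcomes". Section 7.3 builds the notices to sponsor, IRB and regulator on SAEs and unexpected adverse reactions.

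**Order of events on Day 0.** Section 6.3 lists randomization as item 3, the biopsy as item 11 and dosing as item 14: "After all assessments are completed the participant will take the first dose (4 capsules) of the product at the clinic". Section 5.5 gives the same order, with the muscle sample taken before the capsules. Section 6.7.3 says the biopsy is done under local anesthetic.

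**Collection.** Section 7.1.1 has the subject asked at every visit: "Have you experienced any difficulties or problems since I saw you last". Item 1 of the visit lists for Visits 4 to 7 (sections 6.4 to 6.6) names adverse events; the matching item for Visit 3 does not. The Appendix 1 row "Adverse events assessed" is marked at Visits 4 to 7 and blank at Visit 3.

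**Analysis set.** Section 8.2 defines the Safety Population as "all subjects who received any amount of either product, and on whom any post-randomization safety information is available".

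**The concern.** The biopsy is the most invasive procedure in the study, and the protocol foresees its risks. Section 4.2 excludes subjects with lidocaine sensitivity or a bleeding disorder, and section 6.7.3 requires a biopsy screening form and a signed information sheet. Yet half of the planned biopsies take place when the subject has not yet received product, which is the condition the AE definition sets.

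A faint, a bleed or an anesthetic reaction in the interval before dosing could be handled in the clinic and still have no defined place in AE or SAE reporting. The case least well served is a subject affected enough not to be dosed: that person stays outside both the AE definition and the Safety Population. At stake is complete reporting of procedure harm and a clear trigger for expedited notices. The comparison of Niagen with placebo is not affected.

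**Working it through.** **Step 1: how many biopsies precede dosing.** Section 3 gives the base: "The planned sample size for this study is 140 healthy males or females, with 35 subjects randomized equally to each of the four study arms". Section 6.7.3 sets two biopsies per subject, at Day 0 and Day 56.

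- Subjects: 4 × 35 = 140, which matches the stated total.
- Planned biopsies: 140 × 2 = 280 (derived; the protocol does not state it).
- Done before the first dose: 140, and 140 / 280 = 50%.
- If the 20% attrition of section 8.1 all occurs before Day 56: 140 × 0.8 = 112 biopsies at Day 56, 140 + 112 = 252 in total, and 140 / 252 = 56% at Day 0.

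These figures count procedures exposed to the gap. They do not count harms.

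**Step 2: which Day 0 biopsy harms the definition reaches.**

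| Harm | Under 7.1.1 as written |
|---|---|
| Begins after the first dose (for example infection, hematoma, later pain) | AE, whatever the cause; diary and Visit 4 pick it up |
| Begins before the dose and worsens afterwards | Arguably an AE, through the sentence on pre-existing conditions that worsen |
| Begins and resolves before the dose | Not an AE, hence not an SAE under the working criterion of 7.1.2 |
| Occurs in a randomized subject who is never dosed | Not an AE or SAE, and outside the Safety Population |

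The gap is the last two rows.

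**Step 3: whether collection closes the gap.** Section 7.1.1 has the question asked at every visit, so Visit 3 is included; section 6.3 and Appendix 1 leave AE review out of Visit 3. The two cannot both stand. Even if the question is asked at Visit 3, AE review is item 1 wherever it is scheduled, and item 1 comes before the item 11 biopsy. At Visit 4 the question reaches back only to the last contact, that is, the end of Visit 3. The run-in diary is collected at item 7 and the new one handed out at item 12, so no diary is scheduled to be in hand during the biopsy. A subject could write the event down later, but the definition would still not make it an AE.

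**Step 4: how many harms are lost.** The count would be 140 × (complication rate) × (share that falls in the last two rows of the table). The protocol gives no complication rate. It also gives no interval between biopsy and dose from which the share could be judged. The product cannot be evaluated.

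**The case against.** The strongest reply is that the protocol is not silent. The question at every visit covers Visit 3, item 1 of that visit reviews current health status, and diaries run from Visit 2. A faint or bleed in the clinic is seen by the operator. The opening sentence of section 7.1.2 is wide enough to take in a biopsy reaction, and the causality scale in section 7.1.1 has a grade for events with no temporal link to product. Section 4.4 requires the circumstances of any discontinuation to be documented in the participant file and the final report, and section 8.3.1 lists each one with its reason. A Safety Population of dosed subjects suits a comparison of Niagen with placebo.

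Much of this stands, and it rules out three stronger readings that a reader might infer:

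- **That Visit 3 has no AE check at all.** The documents show a conflict between section 7.1.1 and section 6.3 with Appendix 1, which is different from silence.
- **That harms of half of all biopsies go unreported.** Dosing follows at the same visit, and every harm that begins after it counts as an AE. The 50% is a share of procedures.
- **That a subject harmed and never dosed is always missed.** Randomization comes before the biopsy, so that subject appears in the discontinuation documentation.

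What does not stand is the suggestion that nothing needs changing. Being witnessed in the clinic does not make an event an AE, and a discontinuation reason carries no severity grade, causality assessment or SAE trigger. The broad opening of section 7.1.2 leaves the reporting duty arguable when it ought to be plain.

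**Conclusion.** The point holds in a limited form and is worth correcting. On a literal reading, Day 0 biopsy or anesthetic harms that begin and resolve before the first dose, or that occur in a randomized subject never dosed, are not AEs or SAEs and do not clearly trigger the section 7.3 notices. In the never-dosed case they also fall outside the Safety Population. Separately, section 7.1.1 contradicts section 6.3 and Appendix 1 on AE collection at Visit 3.

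Its size is 140 planned Day 0 biopsies exposed to a window within one visit. A reader might multiply 140 by an assumed complication rate of, say, 1% to 5% and report 1.4 to 7 lost events. The protocol does not support that: it gives no rate, and the sum would also require every such event to fall inside the window and be recorded nowhere. The conclusion rests on reading section 7.1.1 literally, on reading section 7.1.2 by its working criterion, and on the Day 0 order in sections 5.5 and 6.3 being followed.

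**What to change.** - **Section 7.1.1:** extend the AE definition to untoward occurrences from the first study procedure at Visit 3, or from consent. Section 7.1.2 and the section 7.3 notices then follow without further change.
- **Section 6.3 and Appendix 1:** reconcile them with section 7.1.1 by adding an AE check at Visit 3, placed after the biopsy, and marking Visit 3 in the AE row.
- **Section 8.3.2:** add a separate listing of pre-dose and procedure-related events, with all biopsied subjects as the denominator. Keep the placebo-versus-Niagen AE table on post-dose events in the Safety Population, so that pre-dose events do not enter the product comparison.

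The cost is one clause, one check at an existing visit, one mark in the schedule and one extra listing, plus a few more recorded events. No visit or sample is added.
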